## Abstract

**Introduction:**

Striking the balance in 24-hour movement behaviour (sedentary behaviour, physical activity and sleep) is expected to reduce the risk of a new major cardiovascular event or death (MACE). We aim to determine the effectiveness and cost-effectiveness of the RISE (*Reduce and Interrupt sedentary behaviour using a blended behavioural intervention to Empower people at risk towards sustainable 24-hour movement behaviour change*) intervention by improving 24-hour movement behaviour for prevention of MACE and gaining quality-adjusted life years (QALYs) in community-dwelling people at risk with a first-ever stroke.

**Methods and analysis:**

This assessor-blinded multicentre randomised controlled trial includes about 1000 participants with a first-ever stroke, of which 752 participants require secondary prevention based on their 24-hour movement behaviour. Participants will be randomly assigned to the experimental group (RISE intervention + usual care) or control (usual care) group. RISE is a 15-week blended care intervention: primary care physiotherapists coach people in their home setting using behaviour change techniques and the RISE eCoaching system. This system consists of: (1) an activity monitor, (2) a smartphone application that provides real-time feedback and contains e-learning modules and (3) a monitoring dashboard for the physiotherapist. A close relative of the participant is involved during the intervention to provide social support. The primary outcome is the effectiveness of the RISE intervention regarding the prevention of MACE measured at one year post randomisation using survival analysis comparing the experimental and control groups. Secondary outcomes include cost-effectiveness for MACE prevention and QALYs and changes in 24-hour movement behaviour over time using compositional data analysis.

**Ethics and dissemination:**

Ethical approval is obtained from Medical Ethics Review Committee Utrecht, NedMec NL83940.000.23. Findings will be disseminated through international peer-reviewed journals and conferences. A sustainable 24-hour movement behaviour change is needed to gain long-term benefits of lowering MACE in patients with stroke. The RISE intervention offers this foundation by integrating behaviour change techniques, the RISE eCoaching system, involvement of participatory support and extensively trained RISE physiotherapists. Consequently, the RISE intervention is expected to be (cost-)effective compared with usual care, and hence, this study will offer a foundation for implementing the RISE intervention in standard poststroke care.

**Trial registration number:**

NCT06124248.

STRENGTHS AND LIMITATIONS OF THIS STUDYThe RISE (*Reduce and Interrupt sedentary behaviour using a blended behavioural intervention to Empower people at risk towards sustainable 24-hour movement behaviour change)* intervention integrates behaviour change techniques, the RISE eCoaching system, participatory support and extensively trained physiotherapists to promote sustainable movement behaviour change.All RISE physiotherapists will complete a 4-day course and participate in the RISE learning community (where RISE-related knowledge or cases will be shared during 3-monthly booster sessions) to ensure RISE intervention quality.The RISE intervention will be delivered in the home setting and is aligned with the existing healthcare system, enhancing its potential for future implementation within usual care.The use of repeated objective measurements will increase statistical power of the study.To address the potential limitation that individuals with limited digital health literacy may struggle to engage with the intervention, the application was co-designed with people with stroke to enhance usability, and participants receive coaching on how to use the RISE eCoaching system.

## Introduction

 Globally, stroke is the greatest contributor to the burden of disease, characterised by a high number of disability-adjusted life years.^1^ The combination of a rising stroke incidence and improvements in acute care has led to a higher number of people living with less residual symptoms after stroke.^2^ However, these people are still at risk of a new major cardiovascular event or death (MACE). A quarter of the people will have a MACE within the first year after stroke.^3^ On top of that, the societal costs incurred by a Dutch stroke patient are high, averaging €29 484 in the first year post stroke.^4^ This stresses the importance of secondary prevention in stroke patients who are at risk for MACE from both the patients’ and societal perspective.

Known risk factors for MACE include an elevated systolic blood pressure, a high body mass index and unhealthy lifestyle factors, such as unhealthy 24-hour movement behaviour (sleep, sedentary behaviour (SB) and physical activity).^5 6^ SB is defined as any waking behaviour with an energy expenditure of ≤1.5 metabolic equivalents, while being in a sitting, lying or reclining posture.^7^ There is increasing evidence that suggests that high levels of SB are strongly adversely associated with cardiometabolic health.^8^ Since the amount of time spent in one behaviour will directly modify the time spent in another, research and interventions should integrate this 24-hour movement behaviour.^9^

Due to its multifactorial nature, changing the 24-hour movement behaviour is a challenging task.^10^ The personal situation, including physical or cognitive capabilities and the (social) environment, varies per individual and therefore requires personalised coaching to enable behavioural change.^10^ Behavioural change is highly needed, since our cohort study showed that 79% of the stroke population was highly sedentary (>9.5 hours) and spent minimal time in moderate to vigorous physical activity (MVPA).^11^ A recent review showed that there are no effective interventions to support community-dwelling stroke patients in reducing SB.^12^ To the best of our knowledge, there are no interventions focusing on specifically targeting the 24-hour movement behaviour in people with stroke.

Given the above, our research group developed the RISE (*Reduce and Interrupt SB using a blended behavioural intervention to Empower people at risk towards sustainable 24-hour movement behaviour change*) intervention, primarily focusing on interrupting SB with at least light physical activity (LPA).^13 14^ The RISE intervention is a blended behavioural intervention, using face-to-face coaching by a physiotherapist (behaviour change techniques) combined with activity monitoring and a smartphone application. As part of the RISE intervention, participants receive social support from someone out of their social network who joins them in the intervention to provide participatory support (PS). Our recent pilot study showed promising results regarding the RISE intervention’s feasibility and preliminary effectiveness, as well as the value of adding PS.^14^

Based on input from healthcare professionals and participants from our RISE pilot study, the RISE intervention and preintervention training of healthcare professionals has been optimised.^10^ In this assessor-blinded multicentre randomised controlled trial, the primary objective is to assess the effectiveness of the RISE intervention to prevent MACE after 1 year compared with usual care according to national stroke guidelines.^15^ Secondarily, the cost-effectiveness of the RISE intervention for MACE prevention and quality-adjusted life years (QALYs) and the effect of the RISE intervention on changes in the 24-hour movement behaviour will be analysed.

## Methods

In this assessor-blinded multicentre randomised controlled trial, participants who require secondary prevention based on their 24-hour movement behaviour (further explained at ‘Study procedures’) will be included and randomly assigned to either the experimental or control group (allocation ratio 1:1) (figure 1). For the protocol, the Standard Protocol Items: Recommendations for Interventional Trials checklist was used, including trial registration details (table 1).

**Figure 1 F1:**
[figure not shown]
Flowchart of the RISE trial. Until one year post randomisation, occurrence of MACE, cost-effectiveness and 24-hour movement behaviour will be measured. All activities with the icon of a house will take place at the participants’ home.

**Table 1 T1:** Trial registration data

Data category	Information
Primary registry and trial identifying number	ClinicalTrials.govNCT06124248
Date of registration in primary registry	08 November 2023 earliest version24 September 2024 last update posted
Secondary identifying numbers	NL83940.000.23 (Medical Ethics Review Committee Utrecht NedMec)
Source(s) of monetary or material support	This work is supported by Dutch Research Council (NWO), Nationaal Regieorgaan Praktijkgericht Onderzoek SIA grant number RAAK-PRO04.093 and Care Research Netherlands & Medical Sciences ZonMW grant number 0930012310010.
Primary sponsor	University Medical Centre Utrecht
Secondary sponsor(s)	N.A.
Contact for public queries	[contact]
Contact for scientific queries	[contact]
Public title	RISE intervention: heading to sustainable movement behavioural change in people with stroke
Scientific title	Secondary prevention by striking the balance in 24-hour movement behaviour by empowering people at risk with a stroke: rationale and design of the RISE intervention randomised controlled trial
Countries of recruitment	The Netherlands
Health condition(s) or problem(s) studied	Stroke
Intervention(s)	Experimental group: RISE intervention and usual care. The RISE intervention is a 15-week blended care intervention: primary care physiotherapists coach people in their home setting using behaviour change techniques and the RISE eCoaching system. This system consists of: (1) an activity monitor, (2) a smartphone application that provides real-time feedback and contains e-learning modules and (3) a monitoring dashboard for the physiotherapist. A close relative from the participant is involved during the intervention to provide social support.
	Control group: usual care
Key inclusion and exclusion criteria	Ages eligible for study: ≥18 years. Sexes eligible for study: both.Accepts healthy volunteers: no
	Inclusion criteria: if people are aged ≥18 years, had a first-ever symptomatic stroke (excluding transient ischaemic attacks) within 6 months before inclusion, are able to walk independently (functional ambulant category ≥3), were independent regarding activities of daily living pre-stroke (Barthel Index >18), are not participating in a physical rehabilitation programme lasting ≥3 months and are discharged to the home-setting.
	Exclusion criteria: if people are unable to understand the Dutch language or have severe comorbidities that withhold them from safely reducing and interrupting their sedentary time
Study type	Interventional
	Allocation: assessor-blinded multicentre randomised controlled trial
Date of first enrolment	November 2023
Target sample size	1000
Recruitment status	Recruiting
Primary outcome(s)	Effectiveness of the RISE intervention regarding prevention of MACE measured at 1 year post randomisation comparing experimental and control groups.
Key secondary outcomes	Cost-effectiveness of the RISE intervention for MACE prevention and quality adjusted life years.Changes in 24-hour movement behaviour (sedentary behaviour, physical activity and sleep) over time between the experimental and control group.

MACE, new major cardiovascular event or death; N.A., not applicable; RISE, Reduce and Interrupt sedentary behaviour using a blended behavioural intervention to Empower people at risk towards sustainable 24-hour movement behaviour change.

### Participants

Participants will be recruited via stroke units in about 30 hospitals in the Netherlands, the general practitioner (GP) clinic or open recruitment between November 2023 and December 2025. They will be approached post discharge in the hospital or via a GP’s letter and asked for permission to share their contact details with the researchers. Open recruitment will occur via articles and flyers, encouraging interested individuals to contact the researchers directly. With participants’ consent, their eligibility will be assessed by consulting the healthcare professional in charge. The number and reasons for non-participation will be recorded.

Participants will be eligible for participation if they are aged ≥18 years, had a first-ever symptomatic stroke (excluding transient ischaemic attacks (TIA)) within 6 months before inclusion, are able to walk independently (functional ambulant category ≥3), were independent regarding activities of daily living pre-stroke (Barthel Index>18), are not participating in a physical rehabilitation programme lasting ≥3 months and are discharged to the home-setting. Participants will be excluded when they are unable to understand and speak the Dutch language or have severe comorbidities that withhold them from safely reducing and interrupting their sedentary time.

### Study procedures

After obtaining informed consent (online supplemental file 1), baseline measurement (T0) takes place at the participants’ home (figure 1). During this visit, an activity monitor will be provided to objectify the 24-hour movement behaviour. If participants require secondary prevention, it will be based on their 24-hour movement behaviour pattern^11^: *sedentary prolongers,* ≥9.5 hours of sedentary time per day, >50% of the sedentary time is spent in bouts >30 min and not reaching the physical activity guideline (150 min MVPA during the week); *sedentary movers,* <9.5 hours of sedentary time and (1) ≤50% of the sedentary time spent in bouts >30 min or (2) not reaching the physical activity guideline.^16 17^ Randomisation will take place for *sedentary prolongers* and *sedentary movers,* with stratification according to these two profiles. All other participants will be excluded after baseline measurement.

Concealment of allocation will be ensured by individual randomisation by an independent researcher. Randomisation to either the experimental or control group will be done using a computer-generated random sequence with block sizes of two, four and six (Castor Electronic Data Capture 2021, Ciwit B.V., Amsterdam, The Netherlands).

The experimental group receives the RISE intervention from a trained primary care physiotherapist for 15 weeks. Follow-up measurements take place at the end of the intervention period (T1) (ie, 4 months post randomisation) and at 6 months (T2), 9 months (T3) and 12 months post randomisation (T4) (figure 1). Due to the nature of the intervention, participants and primary care physiotherapists will not be blinded for treatment allocation. The researcher who performs the measurements at T1 is blinded to treatment allocation.

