### Sample size

The required number of subjects was calculated using the Lachin and Foulkes Logrank Test module in the PASS 2008 software (Hintze J. PASS 2008, Kayesville, Utah, USA www.ncss.com). The power calculation was performed based on detecting a difference in MACE between the experimental and control group. In line with the effectiveness of cardiac rehabilitation, we expect that the RISE intervention will decrease the number of MACE by 35%.^43^ In the control group, 25% is expected to have MACE in the first year.^3 44^ To not underpower the study, an event rate of 20% in the control group in the first year is used. Participants will enter the study during an accrual period of 1.5 years. Enrolment is assumed to be completed for 50% when 50% of the accrual time has passed. A follow-up period of 1 year is assumed to have a 20% loss to follow from the experimental group and a 20% loss to follow from the control group. A two-sided log rank test with a power of 0.85 and a 0.05 significance level to detect a difference of 0.07 between 0.80 and 0.87 (the proportions surviving the experimental and control group after 1 year) led to an overall sample size of 752 participants (of which 376 are in the experimental group and 376 in the control group).

*Sedentary prolongers* and *sedentary movers* will be the target population of the study and will be randomised to the intervention or control group. From our RISE cohort study, we know that 67% of the participants with stroke were *sedentary prolongers* or *sedentary movers*.^11^ Therefore, we expect around 1000 participants need to be screened during baseline measurement (figure 1). Based on our pilot study, we expect to include 2–3 participants per hospital per month. With 20 participating hospitals, this will lead to the expected number of 762 participants by December 2025.

Our secondary outcome, effectiveness of the RISE intervention on reducing SB, can be assessed in a smaller population. From the RISE pilot study, we know that the target group had an average of 11 hours and 21 min of sedentary time per day, with an SD of 77 min/day.^14^ This means, with a two-sided significance level of 0.05, a power of 80%, that a sample size of 47 people per group is needed to detect a minimal detectable change of 45 min in SB between our groups.^45^ Accounting for a dropout rate of 20%, 59 participants per group will be used for this analysis.

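### As written, the sedentary-mover definition randomises people who are favourable on all three movement criteria, which contradicts the stated target population

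*Protocol article*

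**What the plan says.** The opening paragraph of Methods describes those included as "participants who require secondary prevention based on their 24-hour movement behaviour". Study procedures turns this into two profiles based on the baseline activity monitor.

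- The first profile, the prolongers, requires all of the following: "≥9.5 hours of sedentary time per day, >50% of the sedentary time is spent in bouts >30 min and not reaching the physical activity guideline".
- The second profile, the movers, is given as "<9.5 hours of sedentary time and (1) ≤50% of the sedentary time spent in bouts >30 min or (2) not reaching", where condition (2) refers to the same activity guideline as in the first profile.

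Only these two profiles are randomised, "with stratification according to these two profiles". For the rest: "All other participants will be excluded after baseline measurement". Nothing else in the article restates or corrects the rule. The section on the experimental group says that the coaching is meant to make participants sit less and break up their sitting, which fixes the direction in which a pattern counts as unfavourable.

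**The concern.** The prolonger definition treats a large share of sedentary time in long bouts (more than 50%) as adverse. The mover definition uses the opposite side of the same cut-off (at most 50%) as one of two alternative routes into the trial. A good bout pattern thus becomes a sufficient reason for someone under 9.5 hours to be classed as needing prevention.

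The rule controls both entry and stratum. If it is applied literally, the trial enrols some people whose movement behaviour already meets every criterion. It turns away others who differ from them only by a worse bout pattern. The randomised population is then not the one described in Methods, and any effect that works through changed movement behaviour would tend to be diluted. If only the text is wrong, readers still cannot reconstruct eligibility or strata from the publication.

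**Working it through.** The plan gives no figure for this rule that could be reproduced, since no joint distribution of the three criteria is reported. The check is one of logic.

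**Inputs (all from Study procedures).** Let S = at least 9.5 h sedentary per day, B = more than 50% of sedentary time in bouts over 30 minutes, and N = activity guideline not reached. Each is unfavourable by the prolonger definition.

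- Prolonger = S and B and N.
- Mover, natural grouping = not S and (not B or N). The two numbered conditions sit under the 9.5-hour limit.
- Mover, other grouping = (not S and not B) or N.

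**All 2 × 2 × 2 = 8 profiles:**

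| Row | Sedentary time | Share in long bouts | Guideline | Unfavourable features | Natural grouping | Other grouping |
|---|---|---|---|---|---|---|
| 1 | <9.5 h | ≤50% | met | 0 | mover | mover |
| 2 | <9.5 h | ≤50% | not met | 1 | mover | mover |
| 3 | <9.5 h | >50% | met | 1 | not randomised | not randomised |
| 4 | <9.5 h | >50% | not met | 2 | mover | mover |
| 5 | ≥9.5 h | ≤50% | met | 1 | not randomised | not randomised |
| 6 | ≥9.5 h | ≤50% | not met | 2 | not randomised | mover |
| 7 | ≥9.5 h | >50% | met | 2 | not randomised | not randomised |
| 8 | ≥9.5 h | >50% | not met | 3 | prolonger | prolonger and mover |

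**Results.**

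1. Row 1 has no unfavourable feature and is randomised under either grouping.
2. Rows 1 and 3 differ only in the bout share. The better pattern is randomised and the worse one is not. This also holds under either grouping.
3. On the natural reading, row 6 belongs to neither profile and is excluded, with two unfavourable features against none in row 1. This has a different cause: the prolonger profile requires all three features and the mover profile stops at 9.5 hours.
4. The other grouping is no way out. It brings row 6 in, but row 1 stays in and row 8 falls into both strata.

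**Does one small edit settle it?** On the natural grouping, reversing the bout sign in condition (1) makes movers rows 2, 3 and 4. Changing *or* to *and* makes movers row 2 only. Both remove row 1, they define different populations, and neither places row 6. The intended rule therefore cannot be recovered from the article and has to come from its source.

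**The case against.** The strongest reply is that intent and operation are not visible. The profiles are cited to the sponsor's cohort study, the flowchart is not shown, and the bout condition might be meant to describe how a mover typically looks. The randomisation system may already hold a coherent rule. All of this stands as to intent. It does not rescue the text, because a condition offered as an alternative is sufficient on its own, whatever it was meant to describe.

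It is also true that eligibility is settled before allocation and applies to both arms, so the comparison between arms is not biased. What is affected is the definition of the population and, possibly, the size of the effect.

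Three stronger readings are tempting but not supported.

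- *The rule shuts out highly sedentary, inactive people.* Those with more than 50% of sedentary time in long bouts are the prolongers and are randomised. Only the subset at or below 50% is left out. This does not follow from the direction of condition (1), and confining a profile to people with all three features can be a deliberate choice.
- *Movers would hardly exist.* Sample size reports that "the target group had an average of 11 hours and 21 min of sedentary time per day, with an SD of 77 min/day", and a normal distribution would put about 7% below 9.5 hours: (570 − 681)/77 = −1.44. But normality is assumed, and the article does not say that the pilot used the trial's two-profile rule. The Introduction says of the cohort that "79% of the stroke population was highly sedentary (>9.5 hours) and spent minimal time in moderate to vigorous physical activity", which leaves up to 21% outside that group.
- *The excluded subset is 12% or more of the cohort.* Subtracting the 67% classed as prolongers or movers (Sample size) from that 79% gives 12%. This works only if minimal activity in the Introduction means missing the guideline, which the article does not say, and if the 67% was counted under exactly the rule printed here.

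**Conclusion.** The mover definition is wrong as written. It admits a profile with nothing unfavourable, rejects its counterpart with the worse bout pattern, and so conflicts with both the prolonger definition and the population described in Methods. This conclusion needs no distributional assumption and does not depend on how *and* and *or* are grouped.

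The gap at 9.5 hours or more with the guideline missed and at most 50% in long bouts is a separate matter. It arises only on the natural reading, may be intended, and needs confirmation rather than correction by default.

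The size can be given in profiles only: 4 of 8 are randomised, 1 of those 4 being wholly favourable. Profiles are not people, and the article gives neither the joint distribution nor event risks by profile. Neither the number affected nor the loss of effect can therefore be stated. Whether anyone has been enrolled in error depends on the programmed rule, which the article does not show.

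**What to change.** 1. Reconcile the two profile definitions with the cited cohort definition and with the rule programmed for eligibility and stratification.
2. Publish the rule as an eight-row table on sedentary time, bout share and guideline, each row marked prolonger, mover or not randomised. State explicitly how the group at 9.5 hours or more, guideline not reached and at most 50% in long bouts is handled, and confirm that this is intended.
3. If the system already uses a coherent rule, correct the text and stop there.
4. If the literal rule was used, report how many people were randomised or excluded under it, by row. Exclusion follows the baseline measurement, so the classification can be made from data already collected. Keep all randomised participants in the primary analysis and add a sensitivity analysis without the all-favourable profile. That subset is defined by baseline data, so the comparison within it is still between randomised groups.

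The cost is a wording amendment and a check of the randomisation set-up and, only if the literal rule was applied, one tabulation and one extra analysis. The sample size calculation need not be reopened on this ground.
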